### Participants

#### Eligibility and Informed Consent

The participants need to fulfill five conditions. As an initial step for eligibility, participants must be enrolled in an ART program in 1 of the health care centers collaborating in the study. Second, each patient must provide written informed consent confirming their participation in the study. The informed consent includes signed permission to consult their medical records over the duration of the study. Third, participants must be older than 15 years because the focus of the study is on adult PLHIV. Fourth, participants who have been under ART for less than 4 years are preferred, although, experienced patients are also included. We aim at assessing differential effects for individuals initiating ART versus individuals who have been under treatment for a long time. Because the existing literature suggests that drop-out is highest among those initiating treatment, we place more emphasis on individuals who have recently started ART. Therefore, we aim that at least two-thirds of the sample consists of patients that have been under ART for less than 4 years. We trained and informed the health centers and enumerators about this sampling feature. We requested to be informed (by phone) in the case that patients were included, that have been longer on ART. Thus, from the central level we closely monitored the oversampling of patients, who have been under ART for less than 4 years. Fifth, patients must have reliable access to a mobile phone including a stable network connection. Access to a mobile phone is not a major bottleneck: according to the World Factbook there were 12.5 million subscribers in Burkina Faso in 2014, 68 of 100 inhabitants have a mobile phone, and there are 3 major mobile networks that reach out to the entire country [39,40].

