### Sample Size

Power calculations need to account for the stratified nature of the sample. There are 80 treatment centers. We randomly preserve 8 pure control centers to assess spillovers. Within each of the remaining 72 centers, treated and untreated participants are sampled. Thus, for the majority of the centers treatment allocation is not at the level of the center but at the level of the individual. The sample size is calculated with the clustersampsi command of Stata, Version 13 assuming a power of 80% and a significance level of 5%. Furthermore, we impose an intraclass correlation coefficient of 0.015 to quantify the degree to which patients within the same health center are related [45]. We allow for cluster sizes to vary because we know that the size of the eligible population varies across clusters. Thus, we impose a coefficient of variation of cluster sizes of 0.5 (ratio of the standard deviation of cluster sizes to the mean cluster size). Because we collect baseline information we can control for observable characteristics and their correlation with the outcome. We impose a correlation of 0.85. Lastly, because we expect that 35% of the patients will forget to take antiretroviral (ARV) medication from time to time, a target sample size of 3800 PLHIV is needed to obtain a “minimum detectable effect” of an increase in adherence from 65% to 70%. These adherence figures are based on a reported 67% adherence among female PLHIV in Burkina and the government target to bring adherence up to at least 80% [37,38]. As we are conservative about the possibilities of mHealth to raise adherence by 15% the sample was set up in such a way to also identify small gains.

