**Primary outcomes**						
	Retention in care	Dichotomous measure whether a patient remains on ART	X	X	X	X
	ART adherence	Number of doses missed in the past 7 days	X	X	X	X
	Disease progression	CD4 count	X	X	X	X

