### Analysis Plan

Our analysis will exploit the randomized nature of the intervention to attribute treatment effects. In addition to a simple comparison between the pooled treatments and the control group we will also assess the differential impact of the 4 treatment arms. We will employ multivariate regression models to assess the impact of the interventions on each of the primary outcome variables. For the continuous outcome measure (CD4 count) we plan to employ an Ordinary Least Squares model. For the count data (pill doses missed) and if the continuous outcome measure is skewed, we propose to make use of a Poisson model; for the dichotomous outcome (remaining on ARV regimen), we propose to employ a Logit model. In all models we will control for the clustering of participants within health centers.

We will make use of the coefficient estimates from the 4 treatment arms to establish a preference ordering of the effectiveness of the different types (text vs ASCII image) and frequencies (weekly vs semiweekly) of the SMS text message reminders. We will also estimate quantile regressions to identify which group(s) of participants are most (least) likely to have gained from the interventions. Comprehensive data on patient characteristics collected at baseline will allow us to control for confounding factors and patient heterogeneity. These patient characteristics include age, gender, ethnicity, education, whether the patient is the head of the household, income, and whether the patient works. The simple comparison of outcome variables across groups will be complemented by a difference-in-difference identification strategy where we jointly employ the data from the three follow-up surveys. This analysis will permit us to tease out the differences in health outcomes attributable to each of the 4 interventions while controlling for time-fixed effects.

The data will be collected and coded by trained enumerators and analyzed using the statistical and data analysis program STATA. We will use conventional levels of significance at 1%, 5%, and 10%. Because we identified three primary outcome variables we will make use of an inflated alpha when determining significance levels for each and every outcome separately. We apply this correction because the more significance tests we conduct at α=0.05, the more likely we are to claim that we have a statistically significant result. For a significance level of 5% the Bonferroni inflated alpha is 0.05/3 = 0.015.

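### Quantile regression is given the task of showing which patients gained, but it cannot do so; treatment-by-baseline interactions, led by ART duration, can

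*Protocol article*

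**What the plan says.** The Analysis Plan gives quantile regression one purpose: "We will also estimate quantile regressions to identify which group(s) of participants are most (least) likely to have gained from the interventions". It names neither the outcome nor the quantiles.

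The same section assigns a main model to each primary outcome. For CD4, "For the continuous outcome measure (CD4 count) we plan to employ an Ordinary Least Squares model". For retention, "for the dichotomous outcome (remaining on ARV regimen), we propose to employ a Logit model". Missed doses get a Poisson model. Baseline characteristics are mentioned as a means of controlling for confounding and patient heterogeneity; no treatment-by-covariate term is described.

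The outcome table defines retention as "Dichotomous measure whether a patient remains on ART" and adherence as "Number of doses missed in the past 7 days".

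A question about who benefits appears under Eligibility and Informed Consent: "We aim at assessing differential effects for individuals initiating ART versus individuals who have been under treatment for a long time". Recruitment was steered to serve it: "we aim that at least two-thirds of the sample consists of patients that have been under ART for less than 4 years". The Randomization section lists ART duration among the ordering variables, so it is available at baseline. The Summary in the Discussion expects the trial to establish for whom such interventions work.

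**The concern.** The sentence on quantile regression treats a position in the outcome distribution as if it were a group of people. A larger effect at the 10th percentile of CD4 means that the 10th percentile is further apart between arms. It does not mean that patients who would have had low CD4 without messages gained more, and it says nothing directly about women, rural patients or patients new to ART.

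The trial wants to say for whom messages work, and it shaped its sample around one such question. If the only tool named for that purpose cannot answer it, the report may present a quantile profile as evidence about patient groups. The choice of subgroup analyses would then be open to influence from the results.

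**Working it through.** The article gives no figure to reproduce here. The check asks what quantile effects would look like on each primary outcome, and what the alternative would cost in precision.

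**1. CD4, the most favourable case.** Assumed: CD4 without messages normal with mean 450 and SD 200, unrelated to ART duration; two-thirds of patients under 4 years on ART (the recruitment minimum); 1,000,000 simulated patients.

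- World A: early-ART patients gain 45, experienced patients 0. Mean gain = (2/3)(45) + (1/3)(0) = 30.
- World B: early-ART patients gain 0, experienced patients 90. Mean gain = (2/3)(0) + (1/3)(90) = 30.

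| Quantile | Effect in A | Effect in B |
|---|---|---|
| 0.10 | 28.5 | 24.6 |
| 0.25 | 29.5 | 27.0 |
| 0.50 | 30.1 | 30.0 |
| 0.75 | 30.9 | 32.8 |
| 0.90 | 31.5 | 35.6 |

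Both profiles rise gently around 30, although opposite groups gained. The modest difference in slope reflects how widely gains are spread, not who received them. Under the same assumptions, any other characteristic held by two-thirds of patients and unrelated to CD4 would give profile A exactly. An interaction separates the worlds at once: the early-minus-experienced difference is 45 − 0 = +45 in A and 0 − 90 = −90 in B.

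**2. Retention, if the method were applied to it.** A quantile of a 0/1 variable is 0 or 1. With assumed retention of 80% in control and 85% in treated patients, the quantile switches from 0 to 1 at 0.20 and 0.15 respectively. The effect is 1 between 0.15 and 0.20 and 0 everywhere else, which is degenerate.

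**3. Missed doses, if the method were applied to them.** The article gives no share of patients with zero missed doses. As a proxy, take the adherence figures in the Sample Size section, which sets the target "to obtain a “minimum detectable effect” of an increase in adherence from 65% to 70" per cent: 65% zeros in control, 70% in treated. Non-zero counts are assumed to be 1 + Poisson(μ).

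| μ | Share of quantiles with zero effect |
|---|---|
| 0.5 | 92.6% |
| 1 | 90.0% |
| 2 | 85.3% |
| 3 | 83.3% |

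The effect is exactly 0 up to the 0.65 quantile. Above that it is 0, −1 or −2 doses. The method is largely uninformative, but not empty in the upper tail.

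**4. Precision of the interaction.** Let SE be the standard error of the overall treatment effect and p the share under 4 years on ART. With equal outcome variance and equal allocation in both groups, the subgroup standard errors are SE/√p and SE/√(1−p), so the standard error of their difference is

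SE × √(1/p + 1/(1−p)).

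- p = 2/3: √(1.5 + 3) = √4.5 = 2.12.
- p = 0.80: √(1.25 + 5) = √6.25 = 2.50.

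Two-thirds is the minimum aimed for, so 2.12 is the most favourable ratio if that aim was met.

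**The case against.** The best defence is that this is one loosely worded sentence about a supplementary analysis. No main treatment comparison, sample size or significance level depends on it. The authors may mean CD4 only, and a distributional analysis of CD4 is legitimate. That stands, and it limits the weight of the point.

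Several stronger readings are tempting but not supported by the article:

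- **That quantile regression is planned for retention and missed doses.** The article gives those outcomes Logit and Poisson models. The defect is that the outcome is not named, not that a misuse is stated.
- **That the plan expects 65% of patients to miss no dose in 7 days.** The 65% is a sizing assumption about adherence, with no 7-day window attached. It serves above only as a proxy.
- **That the ART-duration question will go untested.** A condensed article may leave subgroup models to the full protocol or analysis plan. What can be criticised is the stated pairing of a method with a conclusion it cannot support.
- **That ART duration is excluded from adjustment.** It is not among the characteristics listed in the Analysis Plan, but that list is introduced as examples and is open.
- **That the interaction must reach about 10.6 points to be detectable (5 × 2.12).** The 5 points refer to a binary adherence proportion, while the planned outcome is a count. The article does not say whether they apply to the pooled or a single-arm comparison, and 2.12 holds only at the minimum split. Only the ratio of standard errors carries over.

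None of this rescues the sentence itself. Even for CD4 alone, quantile effects do not identify groups of participants without rank invariance or treatment-by-covariate terms.

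**Conclusion.** The point holds in this form: the article states a method that cannot support the conclusion assigned to it. This is a flaw in what is written, not a complaint about missing detail. It affects the secondary question of who benefits and leaves the main treatment comparison untouched, so it should be corrected but does not threaten the trial.

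The argument about identification is general and depends on none of the assumed numbers. The CD4, retention and dose figures are illustrations under assumed distributions. The precision ratios of 2.1 and 2.5 assume equal variance and allocation across ART-duration groups. In the Logit and Poisson models they are approximate, because variance there depends on the outcome level in each group. The split actually achieved at recruitment is not reported in the article.

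**What to change.** Replace the quantile-regression sentence with the following:

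- Who gained is assessed by treatment-by-baseline interactions on the pooled-treatment effect, within the planned OLS, Poisson and Logit models and with the planned allowance for clustering by health center.
- The main modifier is ART duration, under 4 years versus 4 years or more, the threshold the article already uses for sampling. Any further modifiers are listed before analysis.
- Effects in each group, and the difference between them, are reported with confidence intervals.
- Quantile regression, if kept, is applied to CD4 only and described as showing how the distribution differs between arms.

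State the limit on power alongside: an interaction standard error about 2.1 times that of the overall effect at a two-thirds/one-third split and 2.5 times at 80/20, so a null interaction must not be read as evidence of equal benefit.

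The cost is wording and a few extra model terms. ART duration was collected before randomization, and the article reports that analysis had not started, so no new data are needed.

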### Objectives

The main objective of this trial is to determine the impact of four different packages of SMS message reminders to promote HIV patients’ retention and adherence to ART as well as their health outcomes in a large-scale randomized controlled trial (RCT) in a Francophone country, namely Burkina Faso. We hypothesize that patients who receive text messages are encouraged to take their pills and reminded of the importance of ART for their health so that they remain in care longer than those who do not receive text messages. We also anticipate that enhanced retention and adherence will lead to positive health outcomes. Our objectives are (1) to inform best practices for enrolling PLHIV into ART programs and supporting them throughout care, (2) to provide insights on the key obstacles confronting patient retention and adherence to ART, (3) to advise on the most effective application of mobile technology for health interventions, including the short-, medium-, and long-term benefits that can be anticipated, and (4) to encourage long-term patient success with ART by promoting feasible and efficient strategies that may be adopted in resource-constrained settings. Concerning the effectiveness of SMS text messaging reminders, our intervention includes two complementary objectives. First, the study evaluates whether patients may experience fatigue from the SMS text messaging reminders. By carrying out 3 surveys at 6, 12, and 24 months after the launch of the intervention, we aim at determining the optimal period for such a type of mHealth intervention to be efficient. Second, the trial will evaluate the effects of message type (text vs ASCII image) and frequency (weekly versus semi- *weekly)*
*,* i.e., the differences in the four treatment arms, on patient outcomes.

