### Study Measures

#### Primary Outcomes

The study focuses on the measurement of three primary outcomes: retention in care, adherence to ART, and disease progression. Retention is measured by a dichotomous variable-whether a patient remains on ART 6, 12, and 24 months after the intervention has started as compared with baseline [46,47]. Retention could have been conceptualized also as the incidence or number of missed visits during a given reference period [48]. However, remaining in care is in itself an important challenge in Burkina Faso. This is in stark contrast to the situation of PLHIV in developed countries. Therefore, we decided to choose remaining on an ART regimen as our retention measure. Adherence or rather lack of adherence to ART is evaluated as the number of doses missed in the past 7 days, which is a self-reported measure [49-51]. It may have been better to use actual pharmacy dispensing data to calculate a medication possession ratio. However, our field experience suggested that it was not always feasible to obtain detailed and correct information about pharmacy dispensing. Contrary to developed countries where standards across hospitals may be similar, in Burkina Faso we observed considerable differences in the standards and routines across health centers both between regions and within them. Because we assess a wide-scale intervention our study also includes rural and remote areas, which are perhaps even less capable of providing this information. Therefore, we opted for inclusiveness knowing that this implies adjustments in the type of comparable indicators that can be collected and analyzed across health centers [51]. Lastly, disease progression is analyzed using patients’ CD4 counts.

Information on these primary outcomes will be collected using individual questionnaires and patient medical records. Table 2 presents details about the indicators with information about the date of data collection.

**Table 2 table2:** Primary and secondary outcome variables.

Classification		Indicators/measures	Baseline	Follow-ups (months after)		
				6	12	24

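### Fixed Bonferroni across the three primary outcomes is valid, but Holm's step-down keeps the same 5% family-wise error and never rejects less

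*Protocol article*

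**What the plan says.** Under Primary Outcomes the protocol article states: "The study focuses on the measurement of three primary outcomes: retention in care, adherence to ART, and disease progression". Under Analysis Plan it says that "we will make use of an inflated alpha when determining significance levels for each and every outcome separately" and gives the figure: "For a significance level of 5% the Bonferroni inflated alpha is 0.05/3 = 0.015". The reason offered is control of false positives: "We apply this correction because the more significance tests we conduct at α=0.05, the more likely we are to claim" a significant result. Results are to be read at the 1%, 5% and 10% levels. No step-down, ordering or passing-on of alpha is described, and confidence intervals are not mentioned.

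Under Objectives the authors expect the outcomes to be linked: "We also anticipate that enhanced retention and adherence will lead to positive health outcomes". The Sample Size section assumes 80% power at a 5% level, for a rise in adherence from 65% to 70%. It gives no effect size for retention or CD4 count.

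**The concern.** Single-step Bonferroni holds every outcome to alpha/3, whatever the other two show. Holm's procedure starts at the same level but relaxes it for the remaining outcomes once one has been rejected. The plan's stated reason for correcting is met equally well by either method, so the fixed level gives up power on the second and third outcomes without gaining any error control.

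This matters because the authors hypothesise effects on all three outcomes, and the trial was sized at 5%, not at the corrected level. A genuine second or third effect could be missed only because it was held to the strictest threshold. The point concerns the family of three that the plan itself defines. It is separate from whether that family should also cover the four arms and the three follow-up waves.

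**Working it through.** **Inputs.** From Analysis Plan: family-wise alpha 0.05, three outcomes, one fixed level each. From Sample Size: 80% power at 0.05, stated for adherence only. Assumed, because the article does not give them: two-sided tests, correlations of 0, 0.3 and 0.5 among the three test statistics, and the power of each outcome (varied below).

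**The plan's own figure.** 0.05/3 = 0.01667, not 0.015. The Šidák level, 1 − 0.95^(1/3) = 0.01695, does not give 0.015 either. Three tests at 0.015 spend at most 3 × 0.015 = 0.045 of the 0.05. The comparison below uses the correct 0.0167; the printed 0.015 would be slightly worse still.

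**Cost of the fixed level for one outcome.** 80% power at two-sided 0.05 means an expected z of 1.960 + 0.842 = 2.802.
- At 0.0167: critical value 2.394, power Φ(2.802 − 2.394) = 65.8%.
- At 0.015: critical value 2.432, power Φ(2.802 − 2.432) = 64.4%.

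**Why Holm keeps the 5%.** Let m0 of the three null hypotheses be true. When the first true null is rejected, at least m0 hypotheses are still in play, so its p-value is at most 0.05/m0. By the Bonferroni inequality, the probability that any of m0 true nulls has such a p-value is at most m0 × 0.05/m0 = 0.05, whatever the correlation.

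**Why Holm never rejects less.** Its thresholds are 0.05/3, 0.05/2 and 0.05, none below 0.05/3. Its first step is identical to Bonferroni, so the chance of at least one rejection is the same under both.

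**Size of the gain.** Simulation with 400,000 trivariate normal draws per scenario; ranges are over correlations 0 to 0.5.

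| True effects (power at 0.05) | Per-outcome power, Bonferroni | Per-outcome power, Holm | All true effects declared, Bonferroni | All true effects declared, Holm |
|---|---|---|---|---|
| One (80%) | 66% | 66% | 66% | 66% |
| Two (80% each) | 66% | 69-70% | 43-51% | 51-57% |
| Three (80% each) | 66% | 73-75% | 29-42% | 50-59% |

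With three unequal effects the gain shrinks:
- Powers of 80/50/30%: 2-3, 6 and 6-8 points for the three outcomes; all three declared 4-10% versus 11-20%.
- Powers of 80/30/15%: about 1, 3-5 and 3-4 points; all three declared 1-3% versus 3-8%.

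With no true effect the family-wise error is 4.5-4.9% under both methods. In no draw did Bonferroni reject an outcome that Holm did not.

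**The case against.** The strongest reply is that nothing here is wrong. Bonferroni over three named outcomes is a recognised, prespecified procedure that does what the plan says it is for. That stands, and it fixes the status of the point. A reader might infer from the power figures that the primary analysis is unsound; the article does not support that, because family-wise error is controlled at 5%, and even the misprinted 0.015 errs on the strict side.

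Second, the largest gain is a best case. A reader might take 8-9 points as the loss in this trial, but the Sample Size section supports 80% power only for adherence, expressed as a proportion, whereas the primary adherence measure is a count of missed doses. CD4 lies downstream of retention and adherence in the authors' own account and may respond more weakly. This stands, and the gain has to be given as a range.

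Third, it is tempting to say that the loss is worst because the outcomes are correlated. The figures say otherwise: with three true effects the gain falls from about 9 points per outcome at correlation 0 to just under 8 at 0.5. What drives it is how many effects are real.

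Fourth, Bonferroni gives simple simultaneous confidence intervals and Holm does not. That is true in general, but the article plans no such intervals, so nothing that it uses is lost.

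Fifth, a fixed threshold can be read off test by test, whereas Holm must rank three specific p-values. The article has several per outcome: three follow-ups, pooled and by-arm comparisons, and a difference-in-difference analysis. This also stands, and the fix has to deal with it.

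**Conclusion.** The point holds as a recommendation on efficiency. The article fixes a single-step rule where one that is never less powerful is available with the same 5% family-wise error. That dominance needs no assumption about correlation or effect size.

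The size of the benefit does need assumptions: two-sided tests, correlations of 0 to 0.5, and 80% power at 0.05 for each true effect. On these it is about 0 points per outcome with one true effect, 3-4 with two and 8-9 with three, and less when powers are unequal. It helps the second and third claims only; the chance of declaring at least one outcome is unchanged. Like the stated Bonferroni, Holm over three outcomes does not cover multiplicity from the four arms or the three waves.

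**What to change.** Replace the fixed level in Analysis Plan by Holm's step-down, and correct 0.015 to 0.0167 in the same sentence. The text should:

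- designate one p-value per primary outcome, for example pooled treatment versus control at one named follow-up;
- compare the smallest of the three with 0.0167, the next with 0.025 and the largest with 0.05, stopping at the first failure;
- scale the steps for the other two reporting levels: 0.0033, 0.005 and 0.01 at 1%; 0.0333, 0.05 and 0.10 at 10%;
- call the level reduced or adjusted, since it is below the nominal one and not inflated.

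No extra patients or data are needed. The real work is choosing the contrast and time point for each outcome. The price is the lack of simple simultaneous confidence intervals. The Results section says that analysis has not begun, so on the article's timeline the change can still be prespecified.

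### The corrected 5% threshold for the three primary outcomes is misprinted: 0.05/3 is 0.0167, not 0.015, and the correction lowers alpha rather than inflating it

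*Protocol article*

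**What the plan says.** The Primary Outcomes section names the family: "The study focuses on the measurement of three primary outcomes: retention in care, adherence to ART, and disease progression". The Analysis Plan section then states the significance levels: "We will use conventional levels of significance at 1%, 5%, and 10" percent. It adds a correction for multiple outcomes: "Because we identified three primary outcome variables we will make use of an inflated alpha when determining significance levels for each and every outcome separately". The reason given is the growing risk of chance findings: "We apply this correction because the more significance tests we conduct at α=0.05, the more likely we are to claim that we have a statistically" (the quote is cut short here). One worked figure follows: "For a significance level of 5% the Bonferroni inflated alpha is 0.05/3 = 0.015".

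This is the only corrected threshold given as a number. The corresponding values for the 1% and 10% levels are not printed, and no other section restates or amends the 5% value.

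**The concern.** A prespecified threshold should give one answer for any p-value. Here the left and right sides of the printed equation disagree, so two analysts who both follow the sentence can use different cut-offs. For a p-value in the gap, they would report different conclusions on retention, adherence or CD4 count at the corrected 5% level. If the choice were made only after the p-value was known, it would become a discretionary decision on a primary outcome.

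The label adds a smaller difficulty. The article calls the result an *inflated* alpha, yet both the formula and the stated reason for the correction require a smaller alpha for each outcome.

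**Working it through.** **Inputs.** Significance level 0.05 and divisor 3, the number of primary outcomes (Analysis Plan; Primary Outcomes confirms the three). Printed threshold 0.015 (Analysis Plan).

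**1. Reproduce the printed figure.** Bonferroni: alpha/m = 0.05/3 = 0.016667. The printed 0.015 is not reproduced.

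**2. Look for a variant that gives 0.015.**

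| Variant | Result |
|---|---|
| Rounded to three decimals | 0.017 |
| Rounded to two decimals | 0.02 |
| Truncated to three decimals | 0.016 |
| Šidák, 1 − 0.95^(1/3) | 0.01695 |
| Divisor 2 | 0.025 |
| Divisor 4 | 0.0125 |
| Divisor 5 | 0.01 |

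None gives 0.015.

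**3. Width of the disputed band.** 0.016667 − 0.015 = 0.001667. For a two-sided normal test (two-sidedness is an assumption), the critical values are 2.432 at 0.015 and 2.394 at 0.016667.

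**4. Error rate, assuming exactly one test per primary outcome.**
- At 0.015: the sum is 3 × 0.015 = 0.045. If the tests are independent, the rate is 1 − (1 − 0.015)^3 = 0.0443.
- At 0.05/3: the sum is 3 × 0.016667 = 0.05. If independent, 0.0492.
- With no correction, for scale: if independent, 1 − 0.95^3 = 0.1426.

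The printed number is stricter than the formula, so the slip is conservative.

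**5. The other significance levels under the same division.** 0.01/3 = 0.0033 and 0.10/3 = 0.0333. A p-value of 0.016 lies below 0.0333. It meets the corrected 10% level whichever 5% cut-off is used, and it fails the corrected 1% level either way. Only its status at the corrected 5% level is in dispute.

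**6. Direction of the correction.** 0.016667 and 0.015 are both below 0.05. The alpha for each outcome goes down. What would be inflated without the correction is the chance of at least one false positive (0.1426 in step 4).

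**The case against.** The strongest reply is that the intended rule can be recovered. The article names the method, the number of outcomes and the formula, so a careful analyst would compute 0.05/3 and the misprint would change nothing. Nor would anyone following the text raise alpha because of the word *inflated*. Much of this stands, and it is why the point is a minor correction. It does not remove the point, since the printed number is the value a reader is most likely to carry into the analysis.

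A reader might infer more than the article supports in three ways.

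- **That results in the band would be wrongly declared not significant.** This holds only at the corrected 5% level, and only if the printed number is followed. With three significance levels in use, such a result would still meet the corrected 10% level.
- **That the trial's family-wise error is at most 4.5% where 5% was intended.** The 0.045 assumes a single test per outcome. The article plans three follow-up waves, a pooled comparison and an assessment of the four arms. Counting every combination as a test gives 3 × 3 × (1 + 4) = 45, and 45 × 0.015 = 0.675. That count is only an illustration, and a separate analysis plan may name one main test per outcome. It shows that the article itself does not support an overall family-wise figure.
- **That each outcome loses about 1.4 points of power.** A two-sided test with 80% power at 0.05 has a non-centrality of 1.960 + 0.842 = 2.802. Its power is then 65.8% at 0.0167 (2.802 − 2.394 = 0.408) and 64.4% at 0.015 (2.802 − 2.432 = 0.370). But the Sample Size section, "assuming a power of 80% and a significance level of 5" percent, covers only a rise in adherence from 65% to 70%. It states no power for retention, for CD4 count or for the number of missed doses, so the 1.4 points cannot be presented as an effect in this trial.

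**Conclusion.** The error is certain: the article prints 0.015 for a quotient that equals 0.0167, and nothing else in it corrects the figure. The result is an ambiguity over a band 0.0017 wide at the corrected 5% level. It errs on the conservative side, and its size in terms of error rate (0.045 against 0.05) depends on one test per outcome. The term *inflated* is wrong but has no effect on the calculation. The point is worth correcting because it concerns the threshold for the primary outcomes. It gives no ground to doubt control of false positives beyond what the article already leaves open, and it does not bear on the sample size.

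**What to change.** Replace the worked figure with a sentence such as: *At the 5% level, the Bonferroni-corrected alpha for each of the three primary outcomes is 0.05/3 = 0.0167.* Change *inflated alpha* to *corrected (reduced) alpha* in both places in the Analysis Plan. Do not describe the 5% as a family-wise level: across waves and arms, that would promise a control that the article does not claim.

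The cost is one number and one term, with no effect on data, participants or sample size. The Results section reports that analysis had not started, so on the article's own account the correction can be made before any result is seen.
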